**Fig 1 pone.0331992.g001:**
[figure not shown]
SPIRIT schedule of enrolment, interventions, and assessments. Schedule based on the SPIRIT 2013 guidelines showing enrolment, baseline, post-intervention, and follow-up assessments. HADS, Hospital Anxiety and Depression Scale; PSS, Perceived Stress Scale; WHOQOL-HIV BREF, World Health Organization Quality of Life HIV BREF; SF-36, 36-item Short Form Health Survey; ACTG-AQ, AIDS Clinical Trials Group Adherence Questionnaire; BMI, body mass index; BP, blood pressure; HR, heart rate; WHR, waist-to-hip ratio.

**Fig 2 pone.0331992.g002:**
[figure not shown]
CONSORT flow diagram of the study protocol. Diagram illustrating participant identification, screening, eligibility assessment, randomization, allocation, follow-up, and final analysis.

**Fig 3 pone.0331992.g003:**
[figure not shown]
Visual abstract of the study design and outcomes. Graphical summary illustrating the study design, assessment time points, and primary outcome measures.

#### Study setting.

The trial will take place at the ART clinic, All India Institute of Medical Sciences (AIIMS), New Delhi, for screening, enrollment, and randomization. The assessments, interventions, and follow-ups will be conducted at the Center for Integrative Medicine and Research at AIIMS, New Delhi.

#### Participant characteristics for the clinical trial.

Individuals have been diagnosed as people living with HIV (PLHIV) as per the National AIDS Control Organization (NACO) guidelines. Eligible participants must have a recent CD4 lymphocyte count of at least 350 cells/mm³ (measured within the last 3 months), and HIV RNA viral load performed within 6 months below 50 copies/ mL (TND-Target Not Detected). A Karnofsky performance scale of more than 70 and receiving standard antiretroviral therapy (ART) ≥ 6 months with no planned ART changes, provided by the National AIDS Control Organization (NACO) or an equivalent recognized body. Additionally, they must undergo regular clinical follow-ups (at least 1 visit in the last 3 months) at the ART Clinic, AIIMS, New Delhi.

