### Study objective

The trial aims to assess the effectiveness of yoga therapy as an adjunct therapy on psychological parameters (depression, anxiety, and stress), quality of life, and medication adherence of PLHIV on ART at a tertiary care hospital in AIIMS New Delhi, India.

Research Questions:

What is the effect of yoga therapy as an adjunct therapy on Depression and anxiety scores among people living with HIV (PLHIV) on ART?What is the effect of yoga as an adjunct therapy on Quality of Life among PLHIV on ART?What is the effect of yoga therapy as an adjunct therapy on Perceived Stress among PLHIV on ART?What is the effect of yoga therapy as an adjunct therapy on ART medication adherence among PLHIV on ART?

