#### Hypothesis.

The primary hypothesis to be tested is that yoga therapy as an adjunct therapy will lead to a change in depression and anxiety scores among PLHIV on ART therapy as compared to an active control (moderate-to-intensity walk). The secondary hypothesis included that a yoga therapy would lead to changes in all secondary health outcomes and would produce significant changes in medication adherence among PLHIV on ART therapy, as compared to an active control (moderate-to-intense walk).

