#### Medication adherence.

A patient logbook will be given to all participants to assess self-reported physical activity, sleep, exercise duration, medication adherence through pill counts (proportion of doses taken), and attrition rate. A mean medication adherence rate below 95% will be considered suboptimal.

Self-reported adherence: How many times have you missed at least one dosage of your HIV medicine in the last 30 days?” Participants provided a number ranging from 0 to thirty. Based on this response, the “single-item self-reported adherence” for the last month will be calculated using the following method [34].

$$\text{Adherence }(\%)\;=\;\frac{\text{1}-Number\;of\;missing\;days}{\text{3}\text{0}}*\text{1}\text{0}\text{0}$$

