#### Statistical analysis.

The normality of continuous outcomes will be assessed using graphical methods and the Shapiro–Wilk test. Continuous variables will be summarized as mean ± standard deviation (SD) for approximately normally distributed data or median (interquartile range [IQR]) for skewed distributions, and categorical variables as frequency (percentage).

The primary endpoint at 3 months will be analyzed using an ANCOVA model, with the 3-month outcome as the dependent variable, treatment group as the fixed effect, and baseline outcome value included as a covariate. This analysis will provide adjusted between-group mean differences with 95% confidence intervals. Effect sizes will be reported to quantify the magnitude of treatment effects. Secondary outcomes assessed at 3, 6, and 12 months will be analyzed as exploratory. Longitudinal analyses will be conducted using linear mixed-effects models with fixed effects for treatment, time, and treatment × time interaction, and baseline included as an adjustment covariate. Models will be estimated using restricted maximum likelihood (REML). An unstructured covariance matrix will be specified initially; if convergence fails, an AR (1) structure will be adopted. Degrees of freedom will be calculated using the Kenward–Roger method. Robust (sandwich) variance estimators will be applied if model assumptions are violated.

Medication adherence (ACTG questionnaire and self-reported) will be analyzed as a binary outcome using logistic regression. Multivariable logistic regression models will be used to identify independent predictors of adherence, adjusting for relevant demographic and clinical covariates.

All analyses will follow the intention-to-treat (ITT) principle. Missing data will be handled using multiple imputation under a missing-at-random (MAR) assumption. The imputation model will include treatment group, time, baseline and follow-up outcomes, relevant covariates, and treatment × time interactions. A sufficient number of imputations will be generated, and convergence will be assessed using standard diagnostics. Sensitivity analyses using delta-adjusted multiple imputation / pattern-mixture models will be conducted to assess robustness to departures from MAR.

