## Discussion

This randomized controlled trial (RCT) aims to evaluate the efficacy of a structured, validated 12-week yoga intervention that integrates psychological and behavioral components. The life expectancy of PLHIV starting ART has increased markedly over the past 25 years. During this period, the efficacy and side-effect profiles of ART regimens have steadily improved, alongside faster virological suppression and enhanced comorbidity care [37]. Despite these advancements, improved life expectancy must be accompanied by reduced disability and better psychosocial outcomes. Depression is projected to become the leading cause of disability among PLHIV by 2030, contributing significantly to the disease burden through its adverse impact on adherence to treatment, increased mortality and morbidity, rapid disease progression, and several other systemic risk factors [38]. The study is designed with rigorous methodology to generate high-quality evidence on the role of yoga as a complementary therapy in HIV management. Specifically, it will compare yoga to an active control group in terms of its effects on psychological parameters (depression, anxiety, and stress) over a long-term follow-up period. Notably, this will be the first trial to comprehensively assess the pleiotropic effects of yoga on medication adherence, an often overlooked yet critical determinant of sustained virological control.

Previous RCTs have demonstrated that yoga can effectively reduce psychological distress [39,40] and enhance quality of life [41] among individuals living with HIV. Qualitative findings suggest that participants often perceive yoga as a tool for cultivating self-awareness and coping constructively with the physical and emotional challenges of their illness [39]. Building upon this evidence, the present RCT will investigate the physiological mechanisms underlying yoga’s parasympathetic modulation [12] and its potential role in mitigating depression and anxiety by acting on the depression pathways linked to HIV pathophysiology. By examining how yoga influences both psychological and biological mediators of disease, this trial may elucidate mechanisms that can inform refinement of future interventions, enhancing their potency, efficacy, and personalization for maximal benefit in PLHIV.

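### Entry limited to virally suppressed patients makes an adherence ceiling likely, and the yes/no analysis then leaves the research-question-4 comparison probably uninformative about improvement

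*Protocol article*

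**What the plan says.** All references are to the protocol article.

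- **Entry.** The section on participant characteristics says that eligible participants must have "HIV RNA viral load performed within 6 months below 50 copies/ mL (TND-Target Not Detected"), a CD4 count of at least 350, and be "receiving standard antiretroviral therapy (ART) ≥ 6 months with no planned ART changes". It adds that "they must undergo regular clinical follow-ups (at least 1 visit in the last 3 months"). The inclusion list under Eligibility criteria mentions stable ART but does not repeat the viral-load or CD4 limits. Neither section sets an adherence level.
- **Question.** Research question 4 under Study objective asks: "What is the effect of yoga therapy as an adjunct therapy on ART medication adherence among PLHIV on ART"? The Hypothesis section says that yoga "would produce significant changes in medication adherence among PLHIV on ART therapy" compared with the walking control.
- **Measurement.** The Medication adherence section collects pill counts as a share of doses taken, plus a 30-day self-report item. It also states: "A mean medication adherence rate below 95% will be considered suboptimal". The ACTG questionnaire covers the previous four days.
- **Analysis.** Under Statistical analysis, adherence from the ACTG and self-report "will be analyzed as a binary outcome using logistic regression". Pill counts are given no role there. Secondary outcomes are labelled exploratory.
- **Link to viral control.** The Discussion calls adherence "an often overlooked yet critical determinant of sustained virological control" and presents its assessment as a first.

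**The concern.** On the protocol's own reasoning, patients with an undetectable viral load after at least six months of ART are likely to be mostly good adherers. That leaves limited room for the yoga arm to do better than the walking arm. Differences that remain, such as two missed doses against five, are differences of degree. A yes/no variable puts both patients in the same category, so it loses much of what could separate the arms.

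At stake is one of four research questions, and the one that the article presents as its novel contribution. A non-significant odds ratio from this analysis would say little about whether yoga helps adherence, yet nothing in the article limits how such a result may be read.

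**Working it through.** **1. The plan's own sample size.** The inputs in Sample size calculation are a mean difference of 1.54 and an SD of 3.38, so d = 1.54/3.38 = 0.456. A two-sided t-test at α = 0.05 with 80% power needs 76.6, so 77 per arm and 154 in total, as stated. Allowing for 20% attrition, 154/0.8 = 192.5 against the stated 192, which agrees within rounding. This is sized for a difference in means. No expected rate or power is given for adherence.

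**2. Power of the yes/no comparison.** Control-arm rates p₁ are assumed, because the article gives none. The effect taken is that yoga halves the share of non-adherent patients: p₂ = p₁ + (1 − p₁)/2. With p̄ the mean of the two rates:

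power = Φ{[(p₂ − p₁) − 1.96·√(2p̄(1 − p̄)/n)] / √[(p₁(1 − p₁) + p₂(1 − p₂))/n]}

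Example with p₁ = 0.90, p₂ = 0.95, n = 77: the null SE is √(2 × 0.925 × 0.075/77) = 0.0424 and the alternative SE is √((0.09 + 0.0475)/77) = 0.0423. Then (0.05 − 1.96 × 0.0424)/0.0423 ≈ −0.79, and Φ gives about 0.22.

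| Control → yoga | 77 per arm | 96 per arm |
|---|---|---|
| 80% → 90% | 41% | 49% |
| 85% → 92.5% | 31% | 38% |
| 90% → 95% | 22% | 26% |
| 95% → 97.5% | 13% | 15% |

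This approximates the unadjusted comparison in the planned logistic regression.

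**3. The upper limit.** If yoga made every participant adherent, power with 77 per arm would be 99% from a control rate of 80%, 95% from 85%, 82% from 90%, 72% from 92% and 51% from 95%. For 80% power the yoga arm must reach 94.9% against 80%, 97.6% against 85% and 99.8% against 90%. From about 92% upward, 80% power is out of reach with 77 per arm.

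**4. Suppressed is not the same as adherent.** Take 30-day adherence as 1 − missed days/30. (As printed, with 1 − missed days as the whole numerator, no missed days would give 1/30 = 3.3%, which cannot be meant.) One missed day gives 29/30 = 96.7%, above the 95% cut-off. Two give 28/30 = 93.3%, below it. So a suppressed patient can still fall below the cut-off, and the control-arm rate cannot be deduced from the entry criteria.

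**5. Does a graded measure help?** A simulation assumed beta-binomial missed doses out of 30, yoga halving the misses, 77 per arm, and about 77–94% of controls at or above 95% adherence. Power across those scenarios was:

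| Analysis | Power |
|---|---|
| Yes/no at 95% | 14–61% |
| Any miss in four days (a definition that the article does not state) | 7–23% |
| Overdispersed binomial model | 22–79% |
| Rank test | 24–82% |

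The effect here is a halving of missed doses, not of non-adherent patients, so these figures should be compared with each other and not with step 2.

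**The case against.** The strongest case against is that the ceiling is inferred. No adherence level is required at entry, no baseline rate is stated, and the viral load may be up to six months old. Step 4 shows that suppressed patients can fall below 95%. All of this stands, and it rules out several stronger readings that a reader might reach:

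- **That participants are already adherent.** The documents make this likely for most, but do not establish it.
- **That the trial cannot answer question 4, or that a null result is close to guaranteed.** Step 3 contradicts this: a very large effect from 80% or 85% would be found. The question asks about an effect and the hypothesis about changes, so adherence that falls unequally between arms over 12 months would also answer it.
- **That the four-day ACTG recall with a 95% cut-off sharpens the ceiling.** The 95% figure appears with pill counts and self-report, not with the ACTG, and the ACTG section says that patients usually take more than one drug. A patient with a single missed day in 30 is adherent at 95%. If the four-day window caught that miss, the patient could be classed as non-adherent, which loosens the ceiling.

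Two further points are fair. Low power for an exploratory secondary outcome is ordinary, and the trial is sized on something else. A statistical analysis plan that is not shown may give pill counts a role. Neither removes the point, because the article itself fixes the binary scale for the two named measures, and the hypothesis and Discussion claim more for adherence than an exploratory label suggests.

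Finally, the fix keeps the eligibility criteria, so it cannot abolish the ceiling. Step 5 shows a gain, but under assumed distributions.

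**Conclusion.** The concern holds as a likely ceiling made worse by an avoidable choice of scale. For a halving of non-adherence, power with 77 per arm is about 41% if 80% of controls are adherent, 22% if 90% are and 13% if 95% are. It stays below 50% even with all 96 per arm followed up. These figures rest on assumed control rates and on the viral-load limit being applied as the participant-characteristics section states it. If the true rate were well below 80%, the problem would be smaller.

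The comparison is therefore probably uninformative about improvement, but not incapable of showing a difference. The primary endpoint and the sample size of 192 are unaffected.

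**What to change.** 1. Make the main adherence analysis the share of doses taken from pill counts and logbook, or the number of missed doses, compared between arms with a binomial model allowing for overdispersion or with a rank or ordinal method. Fix the choice before data are seen. Keep the binary cut-offs as descriptive.
2. State, with research question 4 and the secondary hypothesis, that the result applies to virally suppressed patients on stable ART, and that a null finding cannot be read as no effect in patients with poor adherence.
3. Make the inclusion list agree with the participant-characteristics section on the viral-load limit, since the population for this claim depends on it.

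Cost: changes to protocol and analysis wording only. Eligibility stays as it is and no new data are collected. The downsides are a measure less simple to report than a percentage adherent, a narrower adherence claim, and a ceiling that is reduced but not removed.

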### Eligibility criteria

The subjects will be screened from the ART Clinic, AIIMS, New Delhi, based on the following inclusion and exclusion criteria.

Inclusion criteria:

aAdult diagnosed with HIV RNA, and on stable Antiretroviral therapy.bAge: 18–50 years.cKarnofsky performance scale of more than 70.

Exclusion Criteria:

aHistory of any uncontrolled or unstable major medical condition, including hypertension, diabetes, heart failure, stroke, and apparent opportunistic infection.bUse of medications such as immunosuppressive or immunomodulatory agents other than ART within the past 6 months.cKnown physical disability related to any musculoskeletal, neurological or other condition that contra-indicates moderate physical activity or the specific yoga practices in the protocol.dAny psychiatric conditions mandating drug therapy.ePregnant and lactating women.fPracticing any form of yoga, meditation, or exercise.gIndividuals eligible but unwilling to provide written informed consent.

#### Standard treatment.

For the current trial, standard treatment is defined as the ART medication prescribed by the treating physician at ART clinic, AIIMS Delhi.

### The yoga intervention arm

The yoga therapy program for the study is based on available evidence demonstrating the positive effects of yoga practices on the mental health and quality of life of PLHIV. An interdisciplinary team at CIMR conducted a group discussion to design a yoga module, based on the current literature and the underlying pathophysiological mechanisms of the disease and its progression. The resulting yoga module was reviewed and validated by 10 experienced yoga professionals from diverse schools of yoga, with expert backgrounds in Bachelor of Naturopathy and Yogic Sciences (BNYS), PhD in Yoga, and MSc in Yoga, each with at least 5 years of clinical experience. The finalized yoga module included breathing practices, loosening practices, asanas, pranayama, and relaxation techniques. To ensure clarity, transparency, and reproducibility, the yoga intervention will be recorded using the TIDieR-Rehab (Template for Intervention Description and Replication) checklist [26]. Detailed checklist given in Table 1.

**Table 1 pone.0331992.t001:** The TIDieR-Rehab (Template for Intervention Description and Replication for Rehabilitation) checklist.

S No.	Item	Description
1.	Brief name	Yoga Intervention
2.	Why	Yoga has demonstrated benefits for psychological well-being and quality of life in HIV-seronegative populations. However, evidence regarding structured yoga interventions for people living with HIV (PLHIV) remains limited.
3.	Who	People living with HIV attending the ART clinic, AIIMS, Delhi
4.	When	The intervention will begin within 7 days of randomization and continue for 12 weeks.
5A.	What – Materials	For the yoga therapy sessions, chairs, bands, yoga mats, and wooden blocks will be used. A PowerPoint presentation supported by a yoga manual for yoga therapists describing the intervention. Video of the complete yoga session and picture-based modules will be also given.
5B.	What – Procedures	Structured Validated Yoga Module
6.	Who provided	The yoga therapy program will be delivered by Yoga therapists, supported, and trained for delivering the intervention by the project team. Yoga therapists/Healthcare providers delivering the program will attend a specific one-day course to be certified to deliver the intervention program to ensure program fidelity.
7.	How	Both delivering face-to-face individually and online, using demonstration methods, study materials, and videos.
8.	Where	The intervention will be given at the C.I.M.R, convergence block, AIIMS, New Delhi.
9.	How much –Session(s) duration/Frequency/ Intervention length	Yoga Program: The 12-week, 36-sessions program is divided into two parts. A. 12 sessions for 4 weeks having 60-minute individually supervised yoga sessions with a yoga. B. 24 sessions for the remaining 8 weeks are 60-minute online therapy sessions. therapist to be done at C.I.M.R. The 12-week program will be supervised by the yoga therapist to ensure that the participants correctly learn the practice of asanas, chanting, or meditation and prevent any possible injuries. The yoga module comprises loosening practices, Asanas, Pranayama, and Relaxation Techniques.
10.	How challenging	The dosage (e.g., frequency, duration, intensity, level of severity) of yoga will be tailored to the participant’s abilities throughout the program to support progression and continuous improvements in symptoms during the 12 weeks. Any changes made during the intervention (e.g., reducing intensity due to participant fatigue) will be recorded and reported.
11.	Regression/Progression	The progression will be guided using the Borg scale of perceived exertion for yoga Practices.[27]
12.A	Personalization – Needs	Participants are first introduced to the Borg scale of perceived exertion scale, which ensures accurate self-rating. During interventions, the Borg scale of perceived exertion scale will be measured at specific points—the beginning, during, and end of each session, as well as selectively during asanas—to ensure that participants stay within the specified effort range. Participants will be asked: “Please rate how hard the activity feels right now by choosing a number from 6 (no effort) to 20 (maximum effort).” Increased RPE scorings (score exceeds 15) prompt a rapid modification of practice intensity for safety. RPE records are kept on session monitoring sheets to help assess adherence, guide progression, and maintain intervention fidelity.
12.B	Personalization – Preferences	Those with limited movement will be given the option of chair yoga/Straps/wooden blocks. The instructor-led sessions will be adapted to each participant’s physical and mental capabilities. The sessions are also designed with cultural and personal comfort level in mind.
13.	Protocol deviations	The program will be tailored to the conditions, characteristics, preferences, progression, and improvements of the participant. Modifications will be made and reported based on the participant’s condition or in case of disease progression during the trial (if any).
14.A	How well – Plan	**Compliance and adherence:** To be compliant with the yoga intervention, every participant must attend at least 27 out of the 36 sessions (75%) Participants will be considered adherent if they attend ≥75% of the scheduled supervised yoga sessions, and the prescribed home-practice minutes as recorded in standardized log-book diaries.
14.B	How well – Actual	Adherence and compliance will be evaluated using class attendance logs, self-reported home practice using log-book, and telephonic calls (every 15 days). Participant’s partners will be invited to join the sessions to enhance their adherence.
15.A	Harms – Plan	Throughout the study, each participant will be closely monitored for any adverse reactions that might result from the yoga intervention, or ART medication and for any signs of disease progression. In the event of adverse reactions or disease progression, the treating physician will use clinical judgement and safety factors to determine whether a participant should continue in the study. Participants will receive proper medical attention and any necessary modifications to the yoga intervention will be implemented in response to disease progression or adverse reactions.
15.B	Harms – Actual	To ensure the safety and wellbeing of every participant in the trial, any adverse occurrences will be recorded, submitted to the ethics committee, and examined.

Detailed description of the yoga intervention using the TIDieR-Rehab (Template for Intervention Description and Replication for Rehabilitation) checklist.

Abbreviations: ART = Antiretroviral therapy; PLHIV = People living with HIV; RPE = Rating of Perceived Exertion; CIMR = Centre for Integrative Medicine and Research.

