### Control group

The control group will be advised to continue standard medical treatment for the same duration, along with 12 weeks of moderate-to-intensity walking (prescribed brisk walk). The duration of prescribed brisk walk will be at least practiced for a duration of 60 minutes, 3 times/week, divided into three phases: 8-minutes warm-up, 20–25 minutes of brisk walking, and followed by a 15 minutes cool-down and supine rest. Providing moderate-to-intensity walking in the control arm is intended to ensure the candidates’ interest in continuing in the control arm, reduce attrition in the control group, and not limit them from potential risk-reduction practices. Both groups will be given a logbook to track their sleep, physical activity, and medication intake. For more details, see S1 Annexure.

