### Sample size calculation

The sample size was determined based on a previous study, taking into account an expected mean difference of 1.54 and a pooled standard deviation of 3.38 [36]. The sample size is calculated for a two-sided independent-samples t-test to detect a standardized effect size (Cohen’s d) of 0.455, with a two-sided significance level α = 0.05, power 80%, and equal allocation (N₂/N₁ = 1). The required sample size is 154 participants (77 per group). After accounting for a 20% attrition rate, the adjusted sample size is 192 (96 participants per group).

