### Randomization

Once consented, and after baseline assessment, eligible participants will be randomized (1:1 allocation ratio) using permuted block randomization. A priori, a computer-generated randomization schedule prepared by an independent statistician in randomized, permuted block lengths. Variable block sizes (4, 6, or 8) are used to ensure group balance throughout the study and minimize predictability. Multiple small block sizes are chosen to limit the risk of anticipating the next group assignment while ensuring overall group balance throughout the trial. Allocation numbers will be concealed in opaque sealed envelopes, only accessible to the study staff. The envelopes will be opened after informed consent and baseline assessment. Blinding will be maintained for the outcome assessor and statistician analyzing the data, who will be unaware of group assignments. Baseline evaluations will be done by the nursing staff, and then the randomization will be done by separate C.I.M.R. staff who will not be part of the assessment or intervention.

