### Criteria for dropout or early termination

#### Intervention Completion threshold.

Dropout will be considered if participants attend less than 27 sessions of a total of 36 sessions, being categorized as noncompliant, and will be included in an intention-to-treat analysis (ITT). ITT analysis will include all participants as randomized, regardless of the number of sessions attended, any treatment switches, lost to follow-up due to disease progression (including development of opportunistic infection), or second-line treatment or death. However, such participants will be excluded from the per-protocol analysis. Per-protocol analysis will be limited to participants who meet the adherence threshold, i.e., attending at least 27 sessions.

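### Partners of yoga participants are invited to the sessions with no exception for partners enrolled in the trial, so a walking-arm participant can be invited to the yoga intervention

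*Protocol article*

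**What the plan says.** Under The yoga intervention arm, Table 1, item 14.B lists ways of checking and supporting adherence to yoga and adds: "Participant’s partners will be invited to join the sessions to enhance their adherence". No condition is placed on the partner's own trial status.

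The people who receive yoga are described in item 3 of the same table as "People living with HIV attending the ART clinic, AIIMS, Delhi". The whole trial recruits from that clinic; Eligibility criteria states: "The subjects will be screened from the ART Clinic, AIIMS, New Delhi, based on the following inclusion and exclusion criteria". The list that follows, and the section on participant characteristics before it, do not mention a spouse, partner or household member. The nearest criterion is exclusion f, which bars people who already practise yoga, meditation or exercise.

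Randomization says that "eligible participants will be randomized (1:1 allocation ratio) using permuted block randomization". It names no couple or household unit. Control group gives the other arm a prescribed brisk walk for 12 weeks, not yoga. Intervention Completion threshold fixes the analysis set: "ITT analysis will include all participants as randomized, regardless of the number of sessions attended, any treatment switches".

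**The concern.** Both members of a couple living with HIV can be patients of this clinic and can both meet every listed criterion. With individual 1:1 allocation, about half of such couples would be split between arms. For a split couple, item 14.B applied as worded extends an invitation to the trial intervention to someone allocated to walking. Of the 36 sessions, 24 are online (Table 3), so joining would need little effort.

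The stake is dilution of the primary contrast. An exposed control is still analysed in the walking arm, so any benefit from yoga narrows the difference in HADS-A and HADS-D at 3 months. The per-protocol set is defined by attending at least 27 sessions and has no rule for a control who attended yoga. The sample size allows for 20% attrition and nothing for crossover, and no later analysis can undo the exposure.

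**Working it through.** **Inputs from Sample size calculation.** The plan uses "an expected mean difference of 1.54 and a pooled standard deviation of 3.38", described as a "standardized effect size (Cohen’s d) of 0.455", with two-sided alpha 0.05, 80% power, 77 per group, 20% attrition and 192 randomised (96 per group).

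**Reproducing the plan's own figure.** 1.54 / 3.38 = 0.456. The two-sample t-test with d = 0.455 needs 76.8 per group, hence 77 and 154 in total. 154 / 0.8 = 192.5, against 192 stated. Power at 77 per group is 80.2%. The stated figure reproduces and has no spare margin.

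**Is the route open?**

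- Both partners eligible: no criterion prevents it.
- Split between arms: allocation is individual. The chance that the second member is in the other arm is 96/191 = 50.3%, about one half.
- Control invited: item 14.B has no exception.
- Ordering: if the second partner joins yoga sessions first and is screened later, exclusion f applies and that person is not enrolled. If the future control is enrolled first or at the same time, exclusion f does nothing.

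**Size.** The share of participants who enrol as couples, *f*, is not in the article. I assume 5%, 10% and 20%.

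- Couples = 192 × *f* / 2
- Exposed controls = half of these, one per split couple
- Contaminated share *c* = exposed controls / 96
- Diluted difference = 1.54 × (1 − *c* × *u*), where *u* is uptake times effect: 1 for full attendance with full effect, 0.5 for half
- Power from the two-sample t-test, SD 3.38, 77 per group

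| *f* | Couples | Exposed controls | *c* | Difference, *u* = 1 | Power, *u* = 1 | Difference, *u* = 0.5 | Power, *u* = 0.5 |
|---|---|---|---|---|---|---|---|
| 0% | 0 | 0 | 0% | 1.54 | 80% | 1.54 | 80% |
| 5% | 4.8 | 2.4 | 2.5% | 1.50 | 78% | 1.52 | 79% |
| 10% | 9.6 | 4.8 | 5% | 1.46 | 76% | 1.50 | 78% |
| 20% | 19.2 | 9.6 | 10% | 1.39 | 72% | 1.46 | 76% |

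The *u* = 1 columns are an upper bound for each *f*. They also count couples in the ordering that exclusion f already closes.

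**Effect of the planned ANCOVA.** If 3.38 is the SD of a follow-up score and the baseline to 3-month correlation is *r* (assumed), the residual SD is 3.38 × √(1 − *r*²). With *r* = 0.5, power is about 90% without contamination and 83% at *f* = 20%, *u* = 1. With *r* = 0.4 the corresponding figures are about 86% and 79%.

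**The case against.** The strongest defence is that the article is silent here rather than wrong. It is condensed, and it refers to S1 Annexure, which is not shown, for more detail on both arms. The partner is brought in to support the yoga participant, and a control is reached only through a chain of conditions: both partners live with HIV, attend this clinic, meet the criteria and consent; their trial periods overlap; they fall in opposite arms; and the control accepts. The article supports no frequency for any of these. Attendance logs and the activity logbook would also make such crossover visible.

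Most of this stands as a limit on size. It does not close the route, because both the invitation and the eligibility list are stated without a restriction, and recording a crossover does not prevent it.

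A reader might infer more than the document supports in four respects:

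- **That the rule in effect gives yoga to controls.** It issues an invitation. Attendance and benefit are assumptions.
- **That exclusion f is irrelevant.** It closes one of the possible orderings.
- **That the yoga manual ends up in a control's home.** Item 5A describes the manual as being for the therapists; participants receive video and picture-based material.
- **That correlated HADS scores within couples undermine the models and call for a household random effect.** Under individual allocation, positive correlation lowers the variance of the arm difference for split couples and raises it for same-arm couples. With about half of each, the two largely cancel.

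**Conclusion.** The point holds in a limited form. The plan contains an unrestricted partner invitation that, together with single-clinic recruitment, no couple rule and individual allocation, can bring a walking-arm participant into the yoga sessions. Under intention-to-treat, and if yoga does better than walking, the resulting bias is toward no difference.

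Its size is unknown and probably small. The loss from 80% power to between 78% and 72% rests on three assumptions: 5% to 20% of participants enrol as couples, every split-couple control attends, and each gains the full planned effect. At half uptake or effect the range is 79% to 76%, before any gain from baseline adjustment. The figures do not show that the trial is underpowered. The case for acting is that the plan's own instruction creates the exposure and that removing it costs very little.

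**What to change.** 1. In Table 1, item 14.B, state that a partner who is enrolled in the trial is not invited to the yoga sessions.
2. At screening, ask whether a partner or household member is already enrolled.
3. Where the answer is yes for a partner, apply one pre-stated rule: either enrol only one member per couple, or allocate both members to the same arm.

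The first option in step 3 is simpler. Same-arm allocation keeps the second partner, but that person's arm is then known before enrolment, and there are no split couples left to offset the correlation between same-arm partners.

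The cost is one sentence in the table, one screening question and one line in the eligibility or randomisation text. With the one-member rule, a few second partners are lost and must be replaced from the clinic. Once this route is closed, it gives no reason to change the planned 192.
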